## Abstract

**Background:**

The Refining and Optimising a behavioural intervention to Support Endocrine Therapy Adherence (ROSETA) programme has developed four intervention components aiming to improve medication adherence in women with early-stage breast cancer. These are (a) text messages, (b) information leaflet, (c) Acceptance and Commitment Therapy-based guided self-help (ACT), (d) side-effect management website. Guided by the Multiphase Optimisation Strategy, our pilot trial will use a fractional factorial design to evaluate the feasibility of undertaking a larger optimisation trial. The pilot will include a process evaluation to maximise learning regarding the fidelity and acceptability of the intervention components before proceeding with a larger trial. The trial process evaluation has three aims: to assess the (1) fidelity and (2) acceptability of the intervention components; and (3) to understand participant’s trial experience, and barriers and facilitators to recruitment and retention.

**Methods:**

The process evaluation will use multiple methods. Fidelity of the intervention components will be assessed using self-reported questionnaire data, trial data on intervention component adherence, and observations of the ACT sessions. Acceptability of the intervention components and trial experience will be explored using an acceptability questionnaire and interviews with patients and trial therapists. Trial experience will be assessed using a questionnaire and interviews with participants, while barriers and facilitators to recruitment and retention will be assessed using a questionnaire completed by research nurses and participant interviews. The pilot trial opened for recruitment on 20th May 2022 and was open at the time of submission.

**Conclusions:**

This process evaluation will provide information regarding whether the intervention components can be delivered with fidelity within a national healthcare setting and are acceptable to participants. We will also better understand participant experience in a pilot trial with a fractional factorial design, and any barriers and facilitators to recruitment and retention.

**Registration:**

ISRCTN registry (
ISRCTN10487576, 16/12/2021).

## Introduction

Breast cancer is the most common cancer in the UK
^
1
^. Adjuvant endocrine therapy (AET) is prescribed to women with oestrogen receptor-positive (ER+) breast cancer for 5–10 years to reduce recurrence and mortality
^
2,
3
^. However, up to three quarters of women do not adhere to AET, either taking medication inconsistently or stopping prematurely
^
4–
6
^. Suboptimal adherence can lead to increased risk of recurrence and mortality, reduced health related quality of life, and reduced quality adjusted life years
^
7–
9
^. Multiple factors affect non-adherence behaviours, and these are often described as intentional (
*e.g.*, not believing the medication is necessary, and side-effects), and unintentional (
*e.g.*, forgetting)
^
10–
13
^.

There is a lack of evidence for effective interventions to support medication adherence to AET, with most interventions focusing solely on written educational components, and not targeting the range of barriers to adherence
^
14–
16
^. Moreover, these interventions are typically evaluated using parallel group randomised controlled trials (RCTs). RCTs are able to evaluate whether an intervention package is more effective than a comparator, but they are unable to estimate the contributions of individual components, or the interactions between components. As such, intervention packages demonstrating a statistically significant effect in an RCT could contain ineffective or redundant components, reducing the efficiency of the overall intervention package
^
17,
18
^.

### The ROSETA programme

The Refining and Optimising a behavioural intervention to Support Endocrine Therapy Adherence (ROSETA) programme aims to develop and optimise an intervention package to support adherence to AET in women with early-stage breast cancer. The ROSETA programme is guided by the Multiphase Optimisation Strategy (MOST), which is a framework used to optimise multicomponent behavioural interventions
^
17,
19,
20
^. MOST consists of three stages; (1) preparation, in which intervention components and a conceptual model detailing proposed mechanisms of action are developed, and any pilot testing is carried out, (2) optimisation, in which highly efficient experimental designs, such as factorial designs, are used to estimate the main effects and interaction effects of individual intervention components to build an optimal intervention package, and (3) evaluation, in which the optimised intervention package is compared with a comparator, typically using a parallel groups RCT
^
17,
19,
20
^. 

During the preparation phase of MOST, we combined the intervention mapping framework with MOST to develop four theory-based intervention components targeting distinct, unintentional and intentional barriers to AET adherence: (a) SMS messages to target forgetfulness; (b) information leaflet to target medication beliefs; (c) Acceptance and Commitment Therapy (ACT) guided self-help programme to increase psychological flexibility and reduce psychological distress; (d) side-effect self-management website to target AET side effects
^
21
^ (
Table 1). As part of this preparatory work, we developed a conceptual model for the intervention, detailing the mechanisms of action (
Figure 1). A full description of our approach to intervention development, along with detailed descriptions of the intervention components is available elsewhere
^
21
^.

**Table 1. T1:** Summary of intervention components in the ROSETA pilot trial.

Component	Target	Description	Theoretical basis
SMS	Forgetfulness/habit formation	SMS messages will be sent over 4 months providing practical strategies to support regular medication taking each day. The messages will be sent daily for 2 weeks, twice weekly for 8 weeks and weekly for 6 weeks.	Habit theory
Information Leaflet	Medication beliefs	A written information leaflet containing five elements; an explanation of how AET works with diagrams to supplement, visual displays of the benefits of AET, accurate information about the side effects of AET, answers to common concerns about AET and quotes and pictures of breast cancer survivors.	Necessity Concerns Framework, Common Sense Model of Illness Representations
ACT	Psychological flexibility/psychological distress	A guided self-help intervention based on ACT principles involving four skills; mindfulness, unhooking, following values and living beyond labels. The modules consist of a participant booklet, home practice tasks and audio files. The modules are supported by five individual sessions with a psychologist; 1 x 15 minute opening session, 3 x 25 minute sessions following modules 1, 2 and 3, and 1 x 15 minute closing session following module 4.	ACT (based on relational frame theory)
Website	Side-effect self- management	A website containing strategies to self-manage common AET side effects including; arthralgia, fatigue, vulvovaginal symptoms, gastrointestinal symptoms, hot flushes, sleep difficulties. The website uses a rating system to summarise the strength of evidence for each strategy.	Informed by evidence of side-effect self- management strategies

Key: ROSETA= Refining and Optimising a behavioural intervention to Support Endocrine Therapy Adherence. SMS= Short Message Service. AET= adjuvant endocrine therapy. ACT= Acceptance and commitment therapy.

**Figure 1. f1:**
[figure not shown]
Conceptual model for the ROSETA intervention. This figure has been reproduced with permission from Green
*et al.*, (2023)
^
21
^.

Experimental versions of the intervention components are currently being assessed for feasibility in an external, multi-site exploratory pilot trial, for which a detailed protocol has been published
^
22
^. This pilot trial is using a highly efficient 2
^4-1^ fractional factorial design. Participants are randomised to one of eight experimental conditions, in which they may receive usual care plus a combination of intervention components. Each intervention component has two levels; on or off. Across five UK sites, the pilot trial will recruit approximately 80 women over 18 with stage I-IIIa breast cancer who have been prescribed AET and have completed curative hospital-based treatment. Follow up will be at 2 and 4 months post randomisation. The primary objectives of the pilot trial are to establish eligibility, recruitment, retention and follow up rates, intervention component adherence and availability and feasibility of outcome and process data (ISRCTN: 10487576).

### ROSETA pilot trial process evaluation

Process evaluations of complex interventions can maximise learning from trials, through investigating how an intervention was implemented, clarifying causal mechanisms and exploring contextual factors
^
23
^. As highlighted in the UK Medical Research Council’s (MRC) guidance, process evaluations can have differing functions dependent on the trial stage
^
23
^. In the context of a pilot trial, understanding the feasibility, fidelity and acceptability of an intervention is often the focus, falling within the implementation and context themes in MRC guidance
^
23
^.

The fractional factorial design in the ROSETA pilot trial is uncommon in healthcare research
^
24
^. When used with effect coding (-1, +1), factorial designs can efficiently estimate the main effects and interaction effects of multiple intervention components
^
25
^. However, this design requires multiple experimental conditions, thereby reducing the number of participants randomised to each experimental condition (the condition corresponds to a unique combination of the levels of intervention components). While adequate recruitment and retention of participants is challenging in all healthcare trials
^
26,
27
^, it is particularly important when using factorial designs, as empty cells may threaten the integrity of the trial
^
17
^, or increase complexity in analysis and interpretation. This trial design brings further uncertainties, such as whether multiple intervention components can be delivered with fidelity, participants are not unduly burdened with multiple intervention components, and whether the trial design is acceptable to, and understood by participants. Understanding participant trial experience and exploring barriers and facilitators to recruiting and retaining participants within a factorial design will provide important insights prior to proceeding with a larger optimisation trial. The Theoretical Domains Framework is a helpful tool to understand barriers and facilitators to recruitment and retention. The TDF synthesises 33 theories of behaviour change into factors that could influence behaviour, for example knowledge or available resources
^
28
^.

Intervention fidelity refers to whether an intervention component was implemented as originally intended
^
29
^. Fidelity assessments commonly focus solely on fidelity of delivery of an intervention, with less regard for the fidelity of training, receipt or engagement
^
30,
31
^. The US National Institute of Health Behaviour Change Consortium (NIHBCC) framework suggests fidelity as a multi-faceted construct and recommends five domains of fidelity that should be assessed; design, training, delivery, receipt and enactment
^
32
^. Assessing fidelity at multiple levels can guide targeting of efforts to improve fidelity and hence improve the internal and external validity of a larger trial
^
31,
33,
34
^.

Assessment of acceptability is also recommended in the pilot phase
^
23,
35
^. However, acceptability is frequently assessed as one singular construct, and the definition varies considerably
^
36
^. The Theoretical Framework of Acceptability (TFA) seeks to address this limitation by conceptualising acceptability as a multi-faceted construct consisting of seven components; affective attitude, burden, ethicality, intervention coherence, opportunity costs, perceived effectiveness and self-efficacy
^
36
^. While preliminary work has confirmed the prospective acceptability of the ROSETA intervention components, the pilot trial offers the chance to evaluate acceptability of the intervention components as experienced by intervention recipients, with the potential to improve acceptability prior to a larger optimisation trial.

## Protocol

### Aims and objectives

This process evaluation has three aims: to assess (1) the fidelity of the intervention components; (2) the acceptability of the intervention components; (3) participant’s experience, and barriers and facilitators to recruitment and retention in a fractional factorial trial. These aims address the implementation and contextual factors themes outlined in the MRC framework
^
23
^. The specific objectives for each aim are:

1.Fidelity; Establish the fidelity of each intervention component across five domains of fidelity, guided by the NIHBCC fidelity framework
^
32
^:a.Design. To establish to what extent the intervention components target the behaviour change techniques (BCTs) they are intended to, and to what extent the components are distinct from one another;b.Training. To evaluate the adequacy of therapist training for the delivery of the intervention;c.Delivery. To assess if each intervention was delivered as planned;d.Receipt. To evaluate if participants receive and understand the intervention components they were allocated to;e.Enactment. To understand the degree to which participants implement the intervention components in their daily life;

Identify barriers to the fidelity of training, delivery, receipt and enactment of the intervention components, including any influential contextual factors.

2.Acceptability:a.Assess the acceptability of each intervention component3.Trial experience, recruitment and retention:a.Establish the barriers and facilitators to recruitment and retention of participants;b.Evaluate participant experience of trial participation.

### Design

We will use quantitative and qualitative methods to address the three main aims, nested within the ROSETA pilot trial. The process evaluation will involve assessments with three participant groups; participants of the ROSETA pilot trial, therapists delivering the ACT intervention component, and research nurses (RNs) involved in recruitment.

*
**Fidelity**
*. Fidelity will be assessed in relation to the intended design and delivery, across five domains using a mix of methods.
Table 2 describes the data collection methods for each objective and intervention component, along with the time point at which the data will be collected.

**Table 2. T2:** Summary of fidelity assessments.

Objective	Intervention Component	Data	Data source	Method of completion	Time point
**Design.** To establish to what extent the intervention components target the behaviour change techniques they are intended to, and to what extent the components are distinct from one another.	All	BCTs coded as present in each intervention component, based on the BCTTv1	Independent coder	Independent Coder	Once the trial has commenced
**Training.** To evaluate the adequacy of therapist training for the delivery of the intervention component.	ACT	ACT-FM competency assessment	Questionnaire	ACT trainer	Following therapists first ACT session
	ACT	Number of booster training sessions required	Questionnaire	ACT Trainer	Throughout trial
	ACT	Therapist’s view on ACT training	Semi-structured interview	Therapist	End of trial
**Delivery.** To assess if each intervention component was delivered as planner.	SMS	Delivery of SMS messages	Online System	-	Throughout trial
	SMS	Number of participants opting out	Online System	-	Throughout trial
	Information Leaflet	Number of information leaflets sent	Site Recorded	Research Nurse	Throughout trial
	ACT	Procedural fidelity checklist	Questionnaire	Therapist	After every ACT session
	ACT	ACT-FM therapist stance score	Questionnaire	External rater	End of trial
	ACT	Qualitative data	Semi-structured interview	Therapist	End of trial
	Website	Number of log in details sent	Site Recorded	Research Nurse	Throughout trial
**Receipt.** To evaluate if participants receive and understand the intervention components they were allocated to.	All	Self-reported receipt of intervention component	Questionnaire	Participant	4 months
	All	Self-reported reading of intervention component	Questionnaire	Participant	4 months
	ACT	Session attendance, number of cancelled or missed	CRF	Therapist	After every ACT session
	ACT	Engagement with ACT module materials	CRF	Therapist	After every ACT session
	ACT	Engagement with ACT audio files and home practice tasks	Questionnaire	Participant	4 months
	ACT	Engagement with ACT module materials	Questionnaire	External rater (10% of ACT recordings)	End of trial
	ACT	Printing of ACT module booklet	Questionnaire	Participant	4 months
	Website	Website usage	Website Online System	-	2 and 4 months
	All	Understanding and receipt of the intervention component	Qualitative interview	Participant	End of trial
**Enactment.** To understand the degree to which participants implement the intervention components in their daily life.	All	Qualitative data	Qualitative interview	Participant	End of trial
Identify barriers to the fidelity of training, delivery, receipt and enactment of the intervention components, including any influential contextual factors.	All	Qualitative data	Semi-structured interview	Participants and therapists	End of trial

Key: BCT= Behaviour Change Technique. BCTTv1 = Behaviour Change Technique Taxonomy version 1. ACT = Acceptance and Commitment Therapy. ACT-FM: Acceptance and Commitment Therapy Fidelity Measure. SMS = Short Message Service. CRF = Case Report Form.

Fidelity of design. We will assess whether the intervention components show fidelity to the intended design, in terms of BCTs. BCTs are considered ‘active ingredients’ of behaviour change interventions (e.g. problem solving, action planning). They can be coded using the behaviour change taxonomy version 1 (BCTTv1), which contains 93 BCTs
^
37,
38
^. The research team (SG, SS, LH and CG) have coded which BCTs are present for each intervention component
^
21
^. Two independent coders, external to the research team, will also code the intervention components. Coders will be provided with all intervention component materials and a coding manual and will be asked to identify which BCTs from the taxonomy are present in each intervention component. This process will be conducted once the trial has begun recruitment. The coders will have experience in using BCTs and will have completed BCTTv1 training. They will only code whether a BCT is present or absent, not the frequency of occurrence. Coding from the independent coders will be compared to the original coding
^
21
^, and an agreement coefficient will be calculated
^
39
^. All discrepancies will be discussed between one member of the research team (SG) and the two independent coders, and a final code list will be produced.

Fidelity of training (competency of delivery). The only intervention component to be delivered by healthcare professionals that requires training is the ACT component. Therapists will receive two half days of bespoke training from a clinical psychologist with expertise in ACT (CDG). To establish the adequacy of the training for delivery of the ACT component, a clinical psychologist (CDG) will assess the therapists recording of their first ACT session using the ACT Fidelity Measure (ACT-FM), which assesses therapist fidelity to ACT principles
^
40
^. The number of booster training sessions the therapists require will be monitored. Semi-structured interviews with the therapists will explore barriers to adequate training and scope for any improvements.

Fidelity of delivery. SMS receipt data will indicate whether a message has been successfully sent by the online system. The number of participants who opt-out of the SMS messages will be recorded. The number of information leaflets and website login details successfully sent to participants will be recorded by the site. For the ACT component, therapist scores on a procedural fidelity checklist will indicate which parts of the component were delivered (
*e.g.*, reflection on the utility, relevance and barriers to home practice tasks and introducing the following module). An expert ACT practitioner independent to the trial team will review 10% of all ACT session recordings using the ACT-FM, which assesses therapist fidelity to ACT principles. Reviewed recordings will include those conducted early and late in the trial and from all therapists involved.

Fidelity of receipt. Participants will be asked a single self-reported item to assess which intervention components they received. Self-reported engagement with the intervention component(s) will be collected, along with reasons for non-engagement. For the website, tracking data will be collected, including number of logins, time spent on website, pages visited and videos watched. Each participant will only be asked about the components they were randomised to receive. Semi-structured interviews will investigate fidelity of receipt and elicit any barriers or enablers to the receipt of all intervention components.

ACT therapists will report the number of sessions attended, cancelled or missed by each participant, and the participant’s engagement with module materials (participant manual, associated audio files and home practice tasks). Participant’s engagement with the module materials will also be assessed by an external reviewer assessing 10% of the ACT session recordings.

Fidelity of enactment. Semi-structured interviews will be used to assess the extent to which the participant uses the intervention component(s) in their day-to-day life, and any barriers or facilitators to this.

**
*Intervention component acceptability*
**. The assessment of acceptability of the intervention components will be guided by the TFA
^
36
^ (
Table 3). As described in
Table 3, acceptability will be assessed using an acceptability questionnaire specific to each intervention component at the 4 month follow up
^
41
^, and semi-structured interviews with trial participants and therapists at the end of the trial.

**Table 3. T3:** Summary of acceptability assessments.

Objective	Data	Data source	Method of completion	Time point
Assess the acceptability of each intervention component	Acceptability Questionnaire	Questionnaire	Participant	4 months
	Qualitative data	Semi-structured interview	Participant	End of trial
	Qualitative data	Semi-structured interview	Therapist	End of trial

**
*Trial experience, recruitment and retention*
**. A mix of methods will involve trial participants and RNs (
Table 4). Trial experience will be assessed in participants using a questionnaire assessing experience before, during and after the trial, a single item assessing overall trial acceptability, and during semi-structured interview with questions guided by the TFA
^
36
^. The assessment of the barriers and facilitators to recruitment and retention to the factorial trial will be guided by the TDF
^
28
^. Assessment will include one questionnaire for RNs exploring barriers and facilitators to recruitment, and interviews with participants with questions focusing on any barriers to participation and retention in the trial.

**Table 4. T4:** Summary of trial experience, recruitment and retention assessments.

Objective	Data	Data source	Method of completion	Time point
Evaluate participant experience of trial participation	SPFQ	Questionnaire	Participant	Baseline, 2 months, 4 months
	Acceptability Questionnaire (single item)	Questionnaire	Participant	4 months
	Qualitative data	Semi-structured interview	Participant	End of trial
Establish the barriers and facilitators to recruitment and retention of participants	Recruitment Questionnaire	Questionnaire	Research Nurse	End of trial
	Qualitative data	Semi-structured interview	Participant	End of trial
	Qualitative data	Semi-structured interview	Research Nurse	End of trial

Key: SPFQ= Study Participant Feedback Questionnaire.

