### Data analysis plan

**
*Quantitative analysis*
**

Intervention fidelity. Descriptive statistics will summarise the quantitative intervention component fidelity assessments (
Table 2). For the ACT component, these will also be presented by site. Specific to the fidelity of design assessment, the first-order agreement coefficient statistic (AC1) will estimate the interrater reliability between the independent coders and the BCTs that the components intended to target
^
21,
39
^. Strength of fidelity of design will be defined in terms of pre-established AC1 thresholds; <0.2=poor, 0.2 ≤ 0.4=fairly poor, >0.4 ≤0.6=moderate, >0.6 ≤0.8=good, >0.8 and ≤ 1=very good
^
48
^. Discrepancies will be resolved through discussions between SG and the coders.

Intervention component acceptability. Descriptive statistics will be calculated for the individual items on the acceptability questionnaire, and overall, for each intervention component. Additional questions regarding the acceptability of specific aspects of the ACT and SMS components will be summarised. All summaries will be presented by component. Missing data will be summarised.

Barriers and facilitators to recruitment and retention of participants. Descriptive statistics will be presented for the RN barriers to recruitment and retention questionnaire, alongside qualitative data from the questionnaire. Summaries will be presented overall and by site. Missing data will be summarised.

Participant experience of trial participation. Descriptive statistics will be presented (1) for overall trial experience, and split by experience before starting the trial, during the trial and at the end of the trial; (2) for the one item of the AQ aimed at assessing general acceptability of the trial overall, by experimental condition and by site. Missing data will be summarised.

*

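### The reference list for fidelity of design is described inconsistently (techniques coded as present versus techniques intended), and AC1 on its own does not answer objective 1a under either description

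*Protocol article*

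**What the plan says.** The standard is stated as the intended design in several places. Objective 1a (Aims and objectives, repeated in Table 2) reads "To establish to what extent the intervention components target the behaviour change techniques (BCTs) they are intended to". The Fidelity of design paragraph opens with "We will assess whether the intervention components show fidelity to the intended design, in terms of BCTs". The Data analysis plan (Quantitative analysis, Intervention fidelity) says that AC1 "will estimate the interrater reliability between the independent coders and the BCTs that the components intended to target".

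The method in the Fidelity of design paragraph is worded differently. The research team "have coded which BCTs are present for each intervention component", the external coders "will be asked to identify which BCTs from the taxonomy are present in each intervention component", and "Coding from the independent coders will be compared to the original coding". The coding is present or absent only, from a taxonomy "which contains 93 BCTs".

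The Data analysis plan then grades the strength of fidelity of design by AC1 bands, the top one (very good) running from above 0.8 to 1.

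**The concern.** A list of BCTs that a component was meant to contain and a list of BCTs that someone found in the finished component answer different questions. Agreement between two codings of the same finished materials shows whether coders read those materials alike. It shows whether the materials carry the intended techniques only if the reference list records intention.

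The article uses both descriptions for one statistic and attaches a fidelity grade to it. The stake is whether the evaluation can show that a planned technique did not reach the leaflet, messages, website or ACT materials. That is the question in objective 1a, and the findings are to be used to improve the components.

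**Working it through.** **Step 1. The wording side by side.**

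| Place | Reference for the comparison |
|---|---|
| Objective 1a and Table 2 objective | BCTs intended |
| Fidelity of design, opening sentence | Intended design |
| Fidelity of design, method | The team's coding of BCTs present |
| Data analysis plan | BCTs the components intended to target |

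The method paragraph and the analysis plan cite the same development paper. The article does not say that the two descriptions are one list, or whether that list was specified during development or coded from the finished materials.

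**Step 2. How one omitted BCT scores.** Take a BCT that was intended but never built in, and coders who do not find it.
- Reference is a coding of finished materials, and the team recorded the BCT as absent: absent in both, so agreement.
- Reference is a coding of finished materials, but the team credited the BCT anyway: disagreement, so the omission is exposed.
- Reference is the intended list: disagreement.

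**Step 3. How far AC1 moves.** The plan states no AC1 value, so there is none to reproduce. For one coder against one reference list, AC1 = (pa − pe)/(1 − pe), with pe = 2π(1 − π). Here pa is the proportion of items on which the two agree, and π is the mean of the two proportions marked present.

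Inputs from the article: 93 items, and very good above 0.8. Assumptions, because the article does not give them: scoring over all 93 items, 10 intended BCTs, coders who find exactly what is in the materials, and no unintended BCTs.

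| Missing of 10 | pa | π | pe | AC1, intended list | Intended BCTs found |
|---|---|---|---|---|---|
| 3 | 90/93 = 0.968 | 17/186 = 0.091 | 0.166 | 0.961 | 7/10 |
| 5 | 88/93 = 0.946 | 15/186 = 0.081 | 0.148 | 0.937 | 5/10 |
| 10 | 83/93 = 0.892 | 10/186 = 0.054 | 0.102 | 0.880 | 0/10 |

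If the reference is instead a team coding that correctly records the missing BCTs as absent, pa = 1 and AC1 = 1.00 in every row.

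**Step 4. Range over the assumed list size.** With every intended BCT missing, AC1 against the intended list is 0.943 for 5 intended, 0.880 for 10, 0.811 for 15 and 0.734 for 20. With 20 intended it is 0.853 at 10 missing and first falls below 0.8 at 15 missing (0.790). The many items absent from both lists carry the coefficient.

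**The case against.** The strongest reply is that there is only one list. Both descriptions cite the same paper, which reports intervention development by intervention mapping, so the list may be the developers' own specification. The full protocol that the article summarises may also define it. This stands as far as it goes: a reader might infer that two different lists exist, and the documents do not show that. What remains is that the article gives one statistic two descriptions with different meanings.

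A second reply is that external coders are used precisely to test the team's coding. This also stands. A reader might infer that a comparison with the team's coding can never reveal an unrealised BCT, or that it always flatters the intervention. Neither follows. If the team credited a BCT that outsiders cannot find, AC1 falls. Only an intended BCT that the team itself recorded as absent goes unseen.

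A third reply is that little depends on the figure. Fidelity of design is one descriptive item, discrepancies are discussed to produce a final code list, and the progression criteria in the Discussion rest on consent rates, component adherence and availability of outcome data. That limits the consequence, but it does not make the grade answer objective 1a.

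**Conclusion.** The point holds as an inconsistently described reference combined with a graded statistic that does not answer the stated objective. If the reference is a coding of finished materials, the figure is inter-coder reliability. If it is the intended list, AC1 over 93 items is too insensitive to serve as the grade: with 10 intended BCTs it stays in the top band, at 0.88, when none is found.

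A reader might infer that the choice of list moves the grade from very good to moderate. Scoring only the 10 intended BCTs with 3 missing does give pa = 0.70, π = 0.85, pe = 0.255 and AC1 = 0.445/0.745 = 0.60. But the article describes no such restricted denominator, and the restriction would drop any unintended BCTs the coders find. On the natural 93-item reading the band would seldom change.

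The AC1 values rest on assumed list sizes and accurate coders. The inconsistency in wording needs no assumption.

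**What to change.** Use one reference in both the Fidelity of design paragraph and the Data analysis plan: the BCTs each component was intended to target, as specified at intervention development. For each component, report the number of intended BCTs found out of those intended and the number of unintended BCTs found, beside AC1. Do not grade fidelity of design on AC1 alone.

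If the only list available is a coding of the finished materials, call the statistic inter-coder agreement and drop the fidelity-of-design grading.

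The cost is a wording change and one extra tabulation from coding already planned. The downside is that the reported fidelity figure may look less favourable.
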